##### 6. Satisfaction and Safety of the ReHub System

The experimental patients’ satisfaction with ReHub is measured with the results of the System Usability Scale (SUS) [24]. The questionnaire is also self-administered.

The Physiotherapist-Patient interaction for the experimental group is also measured through the number of messages exchanged between them within ReHub’s chat feature.

The safety of the system will be evaluated with the rate of adverse events reported during the study. Examples of adverse events are minor cutaneous injuries, indentations on soft body parts and software failures.

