**EXCLUSION CRITERIA:**

Any type of disability that could alter the homogeneity of the study leads to exclusion as well as sensory and/or cognitive impairment or concomitant medical conditions which may affect the rehabilitation process. In addition, major medical complications occurring after surgery (e.g. surgical wound infection, suspicious of deep vein thrombosis) also lead to exclusion.

The expected recruitment rate is 2 patients per week.

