### Interventions

Patients are normally discharged 48 hours after the operation with an updated physiotherapy schedule and a leaflet containing the exercises and patterns to follow. The physiotherapist makes sure that the patients (from both groups) have understood them and will perform them correctly.

The rehabilitation program duration per patient is 4 weeks (30 days) after hospital discharge. Three visits take place, one at discharge (baseline), another after 2 weeks and the final visit after 4 weeks (***Table 2***).

**Table 2 T2:** Timepoint chart.

	RECRUITMENT	BASELINE VISIT	INTERVENTION (2 WEEKS)	FOLLOW-UP VISIT	INTERVENTION (2 WEEKS)	FINAL VISIT

**TIMEPOINT**	**-t_o_**	**t_0_**		**t_1_**		**t_2_**

Screening & Eligibility	X					

Informed consent procedure	X					

Treatment randomization	X					

ReHub training (Experimental Arm only)			X			

Timed Up-and-Go		X		X		X

Knee ROM		X		X		X

Muscle strength		X		X		X

Pain level (VAS)		X		X		X

WOMAC		X		X		X

EuroQol-5D-5L		X		X		X

Patient diary data collection (Control Arm only)						X

System Usability Scale (Experimental Arm only)						X

Adherence						X

Adverse events				X		X

The following outcome measures are collected for the patients at the visits:

Active Knee ROM (°) with a goniometer, both flexion and extensionPassive Knee ROM (°) with a goniometer, both flexion and extensionTimed Get-Up-and-Go test (s)Quadriceps muscle strength with a dynamometer (kg)Hamstring muscle strength with a dynamometer (kg)Pain Level with a Visual Analog Scale (VAS)Western Ontario and McMaster Universities Osteoarthritis Index (WOMAC)EuroQol-5D-5L scoreAdherence to exercise program (only collected in last visit)System Usability Scale (only collected in last visit for experimental patients)

Both groups shall perform at home the prescribed exercises. The control group will follow the common home rehabilitation recommendations and exercise autonomously while the experimental group patients will use ReHub to perform their exercises; for both groups the exercise pattern will be the same.

In addition, and as part of the usual hospital protocol, during the last two weeks, the participants of both groups will receive a visit from a physiotherapist from an external company, 2–3 days per week, up to 10 sessions. The details of the intervention for each group are as follows:

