### ReHub telerehabilitation system

ReHub is a digital platform for physical rehabilitation that offers personalized design and monitoring of therapeutic exercise programs to recover the functional capacity of the musculoskeletal system.

The solution is composed of two main pillars; a cloud platform and an exercise kit that includes an inertial motion sensor. The cloud platform establishes communication between the patient and the healthcare professionals in charge of their rehabilitation. It allows physical therapists to create a rehabilitation program specifically tailored to each patient’s condition. A dashboard allows the professional to follow the progress of the patient, see the results of the exercises performed and adapt the program remotely.

Patients use the cloud platform to perform the exercises in their rehabilitation program with the help of DyCare’s proprietary wearable sensor that captures 3D motion data. The sensor is integrated into different exercise tools that help the patient performing different kinds of exercises make up the rest of the kit, though only a body strap is used in this trial as the exercises in the rehabilitation program designed by the hospital do not require additional tools. The sensor records biomechanical parameters such as range of motion and speed in real-time when used on the indicated body part while exercising. When patients do their prescribed exercises at home, intelligent algorithms deliver real-time biofeedback through a User Interface and a Virtual Coach. The results can be viewed by the physiotherapist to follow the progress of the patient, adapt the program remotely if needed or chat with them with the online messaging module through the platform.

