### Sample size estimation and statistical analysis

Sample size estimation was performed considering active knee flexion Range of Motion as the outcome measure. Considering a power of 80%, a two-sided significance level of 0.05 and a dropout rate of 10%, to detect a 10° difference between the two groups, a sample size of 52 patients will be needed. A standard deviation of 12° was determined by previous clinical trials [25,26].

The statistical analysis over the results will be performed by a blinded expert. Within and between-group comparisons will be performed by Two-sample t-test or one-way and two-way ANOVA analysis.

Data will be expressed as mean ± standard deviation (normally distributed data) or median and interquartile range (non-normally distributed data). The threshold for statistical significance will be set to P = 0.05. Missing data will be treated with the Last Observation Carried Forward method.

All statistical tests will be performed with Matlab (The MathWorks, Inc., Natick, Massachusetts, United States) software package.

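### The single adverse event rate used to judge ReHub's safety pools software failures with bodily effects, so it does not separate patient harm from device malfunction

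*Protocol article*

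**What the plan says.** The protocol article, Secondary outcomes, item 6 (Satisfaction and Safety of the ReHub System), sets the measure: "The safety of the system will be evaluated with the rate of adverse events reported during the study". The next sentence illustrates what is counted: "Examples of adverse events are minor cutaneous injuries, indentations on soft body parts and software failures".

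Table 2 (Interventions) has a row "Adverse events", marked at the two-week and four-week visits and carrying no arm label. Rows meant for one arm do carry one, for example "System Usability Scale (Experimental Arm only)". ReHub training is likewise labelled as experimental only and the patient diary as control only.

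On exposure, the article says of the control arm: "The control group will follow the common home rehabilitation recommendations and exercise autonomously". The tablet with ReHub goes only to experimental patients. The section on the ReHub telerehabilitation system says of the exercise tools in the kit, "though only a body strap is used in this trial".

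No section gives an expected adverse event risk, a denominator for the rate or a split by type of event, and none names a test of adverse events between the arms.

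**The concern.** Two of the three examples are physical effects on the patient. The third is a fault of the product. Some software faults may lead to harm, but many will not, and the definition counts them all the same. Someone who follows the text puts a crashed tablet and a skin lesion in one numerator.

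Two consequences follow. Within the ReHub arm, a given rate could consist of crashes, of injuries or of any mixture, and the figure does not tell the reader which. Between the arms, part of the numerator is open to one arm only, because control patients have no software to fail. If the two rates were set side by side, a difference could arise with no difference in harm.

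This is the only safety measure that the article states, and its Discussion foresees that the results could support routine use of such systems after surgery. The measure should be one that can be interpreted.

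**Working it through.** **1. The plan's own figure.** The article states no figure for adverse events. The only planning figure is N = 52, which gives the arm size. Inputs from the sample size section: a 10° difference, SD 12°, and "Considering a power of 80%, a two-sided significance level of 0.05 and a dropout rate of 10%". By the normal approximation, n per arm = 2 × (1.960 + 0.842)² × 12² / 10² = 22.6, rounded up to 23. The total is 46, and 46 / 0.9 = 51.1, rounded up to 52. The stated N reproduces, and 1:1 allocation gives 26 per arm. The point does not touch this figure.

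**2. Which named events can occur in which arm.**

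| Named example | Effect on the patient's body? | ReHub arm | Control arm |
|---|---|---|---|
| Small skin injury | Yes | Possible | Possible |
| Indentation | Yes | Possible | Not from the strap (inferred) |
| Software failure | Not in itself | Possible | Impossible |

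The link between indentations and the strap is an inference: item 6 does not mention the strap, which appears in the description of the system. Only the software failure is both not a harm in itself and impossible in controls.

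**3. Size, under assumed risks.** Let *c* be the risk that a patient has at least one clinical adverse event, equal in both arms. Let *d* be the independent risk of a device event without harm, in the ReHub arm only. The documents give neither; I take *c* = 5%, 10%, 20% and *d* = 10%, 20%, 30%.

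- Pooled risk, control arm: *c*
- Pooled risk, ReHub arm: 1 − (1 − *c*)(1 − *d*)
- Pooled risk ratio: [1 − (1 − *c*)(1 − *d*)] / *c*

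Example: *c* = 0.05 and *d* = 0.30 give 1 − 0.95 × 0.70 = 0.335, and 0.335 / 0.05 = 6.7.

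| *c* | *d* = 10% | *d* = 20% | *d* = 30% |
|---|---|---|---|
| 5% | 14.5%, RR 2.9 | 24.0%, RR 4.8 | 33.5%, RR 6.7 |
| 10% | 19.0%, RR 1.9 | 28.0%, RR 2.8 | 37.0%, RR 3.7 |
| 20% | 28.0%, RR 1.4 | 36.0%, RR 1.8 | 44.0%, RR 2.2 |

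Each cell gives the pooled ReHub risk and its ratio to the control risk *c*. The ratio for clinical events alone is 1.0 in every cell.

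**4. How many failures would produce a nominally significant difference.** The plan names no such test; this only shows scale. Two-sided Fisher exact test, 26 per arm:

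- No clinical events in either arm: 5 ReHub patients with a software failure against 0 give p = 0.051; 6 against 0 give p = 0.023.
- Clinical events in 3/26 of each arm, plus further ReHub patients with only a software failure: 3 more (6/26 vs 3/26) give p = 0.47; 5 more (8/26) give p = 0.17; 7 more (10/26) give p = 0.052; 8 more (11/26) give p = 0.027.

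With some clinical events in both arms, it takes 8/26 = 31% of ReHub patients with a failure and nothing else to cross 0.05. A handful of crashes would not do it.

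**The case against.** The strongest reply is that the plan does not make the comparison. Item 6 is about the safety of the system, and the usability and chat measures beside it are for the experimental arm only. A rate of device-related events in that arm is a legitimate measure and needs no control. The tests named in the statistical section are t-tests and ANOVA, which do not suit an event rate. The missing arm label in Table 2 concerns collection, not analysis. This stands as far as it goes: the between-arm distortion arises only if the arms are compared. Table 2 leaves that open, and the general plan for between-group comparisons makes no exception for safety. The mixing of harm and malfunction remains even when one arm is reported alone.

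A reader might infer more than the text supports:

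- *That the control arm can only score zero.* It cannot have software failures or, by inference, strap indentations. It can have skin injuries and any other reported event.
- *That the rate ignores harm from the exercises, such as falls or a swollen knee.* The three items are introduced as examples, so other events are not excluded. A fuller definition may stand in the full protocol, which is not shown.
- *That indentations should not count.* They are bodily effects, and counting them as adverse events is not wrong.
- *That the pooled rate will hide a real difference in harm.* Nothing in the article rules out a listing by type, in which the events could be told apart.

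**Conclusion.** The point holds in a limited form. The article itself names software failures as adverse events and evaluates safety with one rate that includes them. This is a stated definition, not detail left to another document. The rate mixes patient harm with device malfunction, and a comparison of it between the arms could not be read as a difference in harm.

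The risk ratios of 1.4 to 6.7 are illustrative. They rest on assumed risks, on independence of clinical and device events, and on a patient-level count with 26 per arm; no figure in the documents fixes them. Severity is minor: safety is a secondary outcome with no stated hypothesis or test, and neither the primary analysis nor N = 52 changes.

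**What to change.** Divide the safety outcome in two.

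1. **Patient adverse events, both arms, one definition.** Keep skin injuries and indentations here and flag them as device-related where they are. A software failure that leads to harm enters through the harm. Report the number and percentage of patients with at least one event per arm, and the difference with an exact 95% confidence interval.
2. **Device deficiencies without harm, ReHub arm only.** Report software and sensor failures separately and do not add them to the adverse event rate.

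The cost is a rewording of item 6 and one extra tick-box on the adverse event form. Recruitment was still under way according to the Trial Status section, so events could be classified as they are recorded. The drawback is two safety figures instead of one, the device figure having no comparator.

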### ReHub telerehabilitation system

ReHub is a digital platform for physical rehabilitation that offers personalized design and monitoring of therapeutic exercise programs to recover the functional capacity of the musculoskeletal system.

The solution is composed of two main pillars; a cloud platform and an exercise kit that includes an inertial motion sensor. The cloud platform establishes communication between the patient and the healthcare professionals in charge of their rehabilitation. It allows physical therapists to create a rehabilitation program specifically tailored to each patient’s condition. A dashboard allows the professional to follow the progress of the patient, see the results of the exercises performed and adapt the program remotely.

Patients use the cloud platform to perform the exercises in their rehabilitation program with the help of DyCare’s proprietary wearable sensor that captures 3D motion data. The sensor is integrated into different exercise tools that help the patient performing different kinds of exercises make up the rest of the kit, though only a body strap is used in this trial as the exercises in the rehabilitation program designed by the hospital do not require additional tools. The sensor records biomechanical parameters such as range of motion and speed in real-time when used on the indicated body part while exercising. When patients do their prescribed exercises at home, intelligent algorithms deliver real-time biofeedback through a User Interface and a Virtual Coach. The results can be viewed by the physiotherapist to follow the progress of the patient, adapt the program remotely if needed or chat with them with the online messaging module through the platform.

### Sample size estimation and statistical analysis

Sample size estimation was performed considering active knee flexion Range of Motion as the outcome measure. Considering a power of 80%, a two-sided significance level of 0.05 and a dropout rate of 10%, to detect a 10° difference between the two groups, a sample size of 52 patients will be needed. A standard deviation of 12° was determined by previous clinical trials [25,26].

The statistical analysis over the results will be performed by a blinded expert. Within and between-group comparisons will be performed by Two-sample t-test or one-way and two-way ANOVA analysis.

Data will be expressed as mean ± standard deviation (normally distributed data) or median and interquartile range (non-normally distributed data). The threshold for statistical significance will be set to P = 0.05. Missing data will be treated with the Last Observation Carried Forward method.

All statistical tests will be performed with Matlab (The MathWorks, Inc., Natick, Massachusetts, United States) software package.

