## Methods

### Study design and randomization

The study is a prospective, randomized, controlled, parallel-group, open-label with blinded assessor trial that is conducted according to the SPIRIT recommendations [16]. Following informed consent, patients are randomized (with a 1:1 allocation ratio) to a control group or an experimental group. Computer-generated randomization lists are used (using the website www.randomization.com) to sequentially distribute the patients into one of the two groups. The primary outcome measure is knee Range of Motion (ROM).

The study conforms to the guidelines of the Declaration of Helsinki, was approved by the hospital’s ethics committee (“Comité Ético de Investigación Clínica del HCB”, reg. HCB/2019/0571), and registered at the ClinicalTrials.gov website (identifier NCT04155957).

A flow diagram of the study design is shown in ***Figure 1***.

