### Participants/randomization/allocation/blinding

The general outline of this open-label, parallel-assignment, controlled clinical trial with blinded evaluators is the following: candidates to a TKA with no interfering comorbidities and between 18 and 75 years old will need to sign an Informed Consent Form to be enrolled in the study. The patients then will be randomized with an allocation ratio of 1:1 into one of the two groups: the Control group, receiving the traditional home rehabilitation that patients who undergo Total Knee Arthroplasty (TKA) in a third level hospital (Rapid Recovery Program), or the Experimental group, following the same rehabilitation plan for TKA with ReHub instead of usual autonomous rehabilitation exercices.

Following the allocation of the groups, trained blinded nurses will complete all functional assessments and collect all clinical data on the Case Report Form for each patient. These evaluations will be made at the time of discharge from hospital, after two weeks and after four weeks, both during the follow-up visits.

A total of 52 patients will be recruited following a personal interview carried out by the investigators considering the following inclusion and exclusion criteria mentioned in ***Table 1***.

**Table 1 T1:** Inclusion and Exclusion criteria.

INCLUSION CRITERIA:

1. Age of the candidates shall be between 18 and 75 years 2. Ability to understand and accept the study procedures and to sign an informed consent form 3. Good predisposition to the use of technology or availability of a caregiver providing technological support to the patient 4. Availability to move to the hospital for visits 5. The patient resides in the hospital’s area of influence

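### No named between-group test adjusts for the discharge value, although it is collected for knee ROM and the main secondary outcomes; baseline-adjusted analysis would be a free improvement

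*Protocol article*

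**What the plan says.** The section on sample size and statistical analysis gives one sentence on method, which assigns comparisons both within and between groups to a "Two-sample t-test or one-way and two-way ANOVA analysis". No covariate is named, and it is not said whether follow-up values or changes from baseline are compared.

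On timing, the section on participants and blinding says: "These evaluations will be made at the time of discharge from hospital, after two weeks and after four weeks". Table 2 (Interventions) marks the baseline visit for Timed Up-and-Go, knee ROM, muscle strength, pain, WOMAC and EuroQol-5D-5L. The experimental-group description places delivery of ReHub on the day after discharge, so these values precede the experimental component.

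Other outcomes have no baseline. Adherence and the System Usability Scale are taken at the final visit only. Chat-message counts and adverse events arise during the programme.

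The WOMAC and EuroQol paragraph mentions a later comparison with baseline but names no model.

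**The concern.** In a randomised trial, a baseline measurement of the outcome is usually its best single predictor. A t-test or one-way ANOVA on follow-up values leaves that information unused. There are two consequences:

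- The standard error is larger than it need be, by an amount that depends on the baseline-to-follow-up correlation.
- If the arms happen to differ at discharge, part of that difference stays in the observed treatment estimate.

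With 26 patients per arm, a difference of a few degrees at discharge can arise by chance. A reader of the results would then have to judge informally how much of the week-4 contrast was there before treatment.

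The article does not merely leave the model open. It lists specific tests, and covariate adjustment is not among them.

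**Working it through.** **Inputs from the article**
- Sizing outcome: "Sample size estimation was performed considering active knee flexion Range of Motion as the outcome measure".
- Error rates and dropout: "Considering a power of 80%, a two-sided significance level of 0.05 and a dropout rate of 10" percent.
- Target and total: "to detect a 10° difference between the two groups, a sample size of 52 patients will be needed".
- Spread: "A standard deviation of 12° was determined by previous clinical trials". It is not said whether this refers to the follow-up value or to the change.
- Allocation: "patients are randomized (with a 1:1 allocation ratio) to a control group or an experimental group".

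**Assumptions (not in the article)**
- Correlation r between discharge and follow-up flexion: 0.2 to 0.7.
- 12° is the SD at follow-up, and the SD at discharge is the same.

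**Step 1: reproduce 52.**
n per arm = 2 × 12² × (1.960 + 0.842)² / 10² = 22.6, rounded up to 23. The total is 46, and 46 / 0.9 = 51.1, giving 52 (26 per arm). The figure reproduces with no allowance for baseline adjustment. The t-based version gives 24 per arm and 48 / 0.9 = 53.3, so 54, which is close.

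**Step 2: precision with 23 evaluable per arm.**
- Follow-up values: SD 12, SE = 12 × √(2/23) = 3.54°.
- ANCOVA: residual SD = 12 × √(1 − r²).
- Change scores: SD = 12 × √(2(1 − r)).

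Power for 10° is from the two-sided t-test at 0.05:

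| r | Follow-up: SE, power | ANCOVA: SE, power | Change: SE, power |
|---|---|---|---|
| 0.2 | 3.54°, 0.789 | 3.47°, 0.805 | 4.48°, 0.589 |
| 0.3 | 3.54°, 0.789 | 3.38°, 0.826 | 4.19°, 0.647 |
| 0.5 | 3.54°, 0.789 | 3.06°, 0.891 | 3.54°, 0.789 |
| 0.7 | 3.54°, 0.789 | 2.53°, 0.972 | 2.74°, 0.946 |

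With 23.4 per arm (26 × 0.9) the unadjusted power is 0.796, and ANCOVA gives 0.832, 0.896 and 0.974 at r = 0.3, 0.5 and 0.7. The ANCOVA variance is lower than that of follow-up values by r²: 4%, 9%, 25% and 49% at the four values of r. The degree of freedom spent on the covariate changes power by less than 0.001 here.

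**Step 3: chance imbalance at discharge.**
The SD of the difference between arm means at discharge is also 12 × √(2/23) = 3.54°. The probability that it exceeds 5° in either direction is about 16% (about 13% with all 26 per arm). If a 5° difference occurs:
- a follow-up comparison carries r × 5° = 1.5°, 2.5° or 3.5° at r = 0.3, 0.5 or 0.7;
- a change-score comparison over-corrects by (1 − r) × 5° = 3.5°, 2.5° or 1.5°;
- ANCOVA removes the expected carry-over.

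**Step 4: the other reading of 12°.**
If 12° is the SD of change and changes are compared, ANCOVA has residual SD = 12 × √((1 + r)/2). The variance ratio to change scores is (1 + r)/2 = 0.60, 0.65, 0.75 or 0.85 at r = 0.2, 0.3, 0.5 or 0.7. Adjustment still helps, but the gain is then largest at low r.

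**The case against.** **The planned test is valid.** This stands in full. Randomisation makes the unadjusted comparison unbiased, its type I error already allows for chance imbalance, and 52 is consistent with it. A reader might infer from this point that the primary analysis is biased or the trial wrongly sized; the article supports neither inference.

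**The plan may not disregard baseline.** This stands in part. A two-way ANOVA of group by visit could include the discharge visit, and the WOMAC and EuroQol paragraph refers to baseline. It would therefore be too strong to say that the plan ignores baseline. But the group-by-visit interaction tests differences in change, and the group main effect averages in a visit before the intervention. Neither is covariate adjustment, and the WOMAC and EuroQol remark does not cover the primary outcome.

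**Not every outcome has a baseline.** Correct. Adherence, the usability scale, chat counts and adverse events cannot be adjusted in this way.

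**The gain may be slight.** Correct. At r = 0.2 power moves from 0.789 to 0.805. The article gives no r and does not say what its 12° describes, so no single figure can be claimed. Nor is a material imbalance probable: a difference above 5° has roughly a one-in-six chance, and only a fraction r of it carries into follow-up values.

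**Covariates are usually left to the analysis plan.** This would answer a silent protocol. Here the article names the tests, so an unseen analysis plan that used ANCOVA would depart from them.

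**Discharge values are taken after randomisation.** This is no obstacle, because they are taken before ReHub is delivered and so can serve as a covariate.

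**Conclusion.** The point holds as a free improvement, not as an error. No named between-group test adjusts for the discharge value, although that value is available for knee ROM, Timed Up-and-Go, muscle strength, pain, WOMAC and EuroQol-5D-5L.

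If 12° is the SD of follow-up flexion and about 23 patients per arm are evaluable, adjustment raises power for 10° from 79–80% to about 81% (r = 0.2), 83% (0.3), 89–90% (0.5) or 97% (0.7). It also removes the expected carry-over of any chance difference at discharge. The direction of the benefit does not depend on which reading of the SD is right. Its size does, and it also depends on an unknown correlation, so the benefit may be modest.

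**What to change.** Replace the sentence on between-group comparisons with a statement along these lines: for each continuous outcome measured at discharge, the treatment effect is the difference between arms at follow-up, estimated by ANCOVA (or a repeated-measures model over the two follow-up visits) with that outcome's discharge value as covariate, and reported with a 95% confidence interval. State that adherence, the System Usability Scale, chat counts and adverse events have no baseline and are analysed without this adjustment.

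The sample size need not change. The cost is wording only: the discharge data are already scheduled. The Trial Status section reports that recruitment and data collection are ongoing, so the model can be fixed before the analysis.

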**Methods/design::**

The study is a randomized, open-label with blinded outcome assessor, parallel assignment clinical trial with a sample size of 52 patients that is conducted according to the SPIRIT recommendations. After the TKA intervention, the patients are randomly allocated to the control group or the experimental group with a 1:1 ratio. Both groups follow a Fast Track recovery protocol which includes discharge after 2–3 days from surgery, a daily plan of 5 exercises for autonomous rehabilitation and domiciliary visits by a physiotherapist starting approximately 2 weeks after surgery. The experimental group uses the sensor-based telerehabilitation system ReHub to perform the exercises. The primary outcome measure is the range of motion of the knee. Secondary outcomes include physical performance, quality of life, pain intensity, muscle strength, treatment adherence and satisfaction with the ReHub system. The outcomes assessment is performed at hospital discharge (baseline), at stitch removal (2 weeks after baseline) and 2 weeks after stitch removal (4 weeks after baseline).

The study conforms to the guidelines of the Declaration of Helsinki and was approved by the hospital’s ethics committee.

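### Last observation carried forward is the only missing-data rule for an outcome measured during recovery; it attenuates a true effect, costs some power, and can create a false difference if dropout is unequal

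*Protocol article*

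**What the plan says.** Under *Sample size estimation and statistical analysis* the protocol article states: "Missing data will be treated with the Last Observation Carried Forward method". The sentence is not limited to any outcome, and no alternative or sensitivity analysis accompanies it. The same section plans t-tests or ANOVA for the group comparisons.

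The visit schedule is in the abstract, under *Methods/design*: "The outcomes assessment is performed at hospital discharge (baseline), at stitch removal (2 weeks after baseline", with a last assessment at week 4. The *Background* puts discharge at 48 to 72 hours after surgery. The values available to carry forward are therefore a knee measured 2 to 3 days after the operation or one measured at about 2 weeks.

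The sample size rests on active knee flexion: "Sample size estimation was performed considering active knee flexion Range of Motion as the outcome measure". Its inputs are "Considering a power of 80%, a two-sided significance level of 0.05 and a dropout rate of 10" per cent, then "to detect a 10° difference between the two groups, a sample size of 52 patients will be needed", and "A standard deviation of 12° was determined by previous clinical trials".

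**The concern.** The method is unbiased for a patient's missing later value only if nothing would have changed after the last visit attended. Here change over those weeks is the purpose of the programme. Four consequences follow.

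- A dropout enters the week-4 comparison with an early value. If the treatment effect builds up over time, that value holds little or none of it, so the estimated difference shrinks.
- Mixing early and late values within an arm widens the spread and lowers power.
- The t-test or ANOVA treats filled-in values as measured, with no allowance for their uncertainty.
- If one arm loses more patients than the other, more of its values are early ones, and a difference appears that treatment did not cause. Unequal loss is possible because the trial is open-label and only the experimental arm receives the device, daily remote monitoring and site-team home visits (*Interventions*). The article does not predict it.

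The rule also works against the trial's own sizing. The dropout allowance treats lost patients as giving no data, whereas the analysis puts them back with early values.

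**Working it through.** **Inputs from the article:** difference 10°, SD 12°, two-sided 0.05, power 80%, dropout 10%, 1:1 allocation, N = 52.

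**Assumptions, because the article gives no means by visit:**
- Week 4 is the analysed visit.
- Dropout is unrelated to outcome.
- g is the control arm's mean gain from the carried visit to week 4.
- e is the arm difference already present at the carried visit. The experimental gain is then g + 10 − e.

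**1. The plan's own figure.** n per arm = 2 × (1.96 + 0.84)² × 12² / 10² = 22.6, so 23. Then 23 / 0.9 = 25.6, so 26 per arm and 52 in total. This matches. A t-test on 23 observed patients per arm has power 79%, the benchmark below.

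**2. Formulas with dropout d = 0.10 in each arm.**
- Expected difference = 10 − d × (10 − e).
- Variance in an arm = 144 + d(1 − d) × (gain in that arm)², where d(1 − d) = 0.09.
- SD = square root of the mean of the two variances. Power is from the two-sample t-test with 26 per arm.

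**3. Week-2 value carried, half the effect present (e = 5).** Difference = 10 − 0.1 × 5 = 9.5°.

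| g | Control variance | Experimental variance | SD | Power |
|---|---|---|---|---|
| 5° | 144 + 0.09 × 5² = 146.25 | 144 + 0.09 × 10² = 153.00 | 12.2 | 78% |
| 10° | 153.00 | 164.25 | 12.6 | 76% |
| 15° | 164.25 | 180.00 | 13.1 | 73% |

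**4. Discharge value carried for every dropout, no arm difference at discharge (e = 0).** Difference = 10 − 0.1 × 10 = 9.0°.

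| g | Control variance | Experimental variance | SD | Power |
|---|---|---|---|---|
| 15° | 144 + 0.09 × 15² = 164.25 | 144 + 0.09 × 25² = 200.25 | 13.5 | 65% |
| 20° | 180.00 | 225.00 | 14.2 | 61% |
| 25° | 200.25 | 254.25 | 15.1 | 56% |
| 30° | 225.00 | 288.00 | 16.0 | 51% |

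A simulation of 40,000 trials per setting (within-patient correlation 0.6) agrees: 61% at g = 20° and 52% at g = 30° with discharge carried, and 79%, 76% and 73% at g = 5°, 10° and 15° with week 2 carried.

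**5. Unequal dropout, discharge carried, no true effect.** Shift = g × difference in dropout proportions. For 4 of 26 against 1 of 26, this is g × 3/26: 15 × 3/26 = 1.7° and 30 × 3/26 = 3.5°. The arm with more dropout looks worse. In the simulation, a 5% against 15% split gave shifts of about 2° and 3° at g = 20° and 30°, with two-sided type I error of 8% and 10%.

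**6. Equal dropout, no true effect.** The simulated shift is zero within simulation error, and type I error stays at about 5%.

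**The case against.** The strongest reply is that the discharge-carried figures describe an unlikely pattern of loss. The week-2 assessment coincides with stitch removal, which patients need for their care whether or not they are in the trial. The inclusion criteria also require residence in the hospital's area and availability to travel there. Loss between weeks 2 and 4 is the more natural pattern, and the power loss is then modest: about 78% to 73% against 79%. Only about 5 of 52 patients are involved. This stands, and step 4 should be read as a worst case.

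It is also fair that the recovery gain is not in the article. A reader might infer that a steep recovery curve is documented; it is not, and each power figure above depends on an assumed g.

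A reader might further infer that the rule biases the primary comparison in all circumstances. It does not. With equal dropout and a true effect, the bias is towards no difference, by 0.5° to 1°. A raised false-positive rate needs unequal loss, and the splits in step 5 are illustrations. Greater loss in the control arm can even inflate the estimate without costing power.

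Finally, adherence and the System Usability Scale are collected only at the last visit, so nothing can be carried. This is minor: the rule simply does not apply to them, the usability scale has no between-arm comparison, and experimental-arm adherence comes from the device database.

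What the reply does not do is make the rule a good choice. In the equal-dropout settings of steps 3 and 4, analysing the observed patients does as well or better.

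**Conclusion.** The point holds at moderate size and should be fixed. The sample size of 52 is not wrong. The fault is a missing-data rule that assumes no further recovery in a trial about recovery, stated as the only method. With balanced 10% dropout it turns a true 10° into 9.5° (power about 78% to 73%) if week-2 values are carried, and into 9.0° (about 65% to 51%) if every dropout is carried from discharge. With dropout of 4 against 1 per 26 and discharge values carried, the shift is 1.7° to 3.5°. These ranges rest on assumed control gains of 5° to 15° after week 2 and 15° to 30° after discharge. The 79% benchmark from observed values assumes that loss is unrelated to outcome. A reader might infer from the worst case that the trial is likely to have only about half power; the article does not support that, since it gives neither the trajectory nor the timing of losses.

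**What to change.** Replace the sentence for the primary outcome. Use a likelihood-based repeated-measures model on all observed visits, with baseline adjustment and without single imputation. Multiple imputation followed by a baseline-adjusted comparison is an acceptable alternative. Keep the carried-forward analysis, if at all, as a labelled sensitivity analysis. Report the single-visit outcomes (adherence and the System Usability Scale) as observed.

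No patients or visits are added. The cost is a documented wording change and slightly more analysis work. The new method relies on data being missing at random, so add a sensitivity analysis that departs from that assumption. *Trial Status* describes data collection as ongoing, and the plan calls for a blinded analyst, so the change can still be made credibly if it is recorded before unblinding.
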